#### Data analysis

The descriptive statistical methods employed in this study will depend on the nature of the analyzed variables. For qualitative variables, the following descriptive statistics will be computed: frequency and percentage. Quantitative variables will be presented using measures of central tendency and dispersion.

For univariate statistical analysis of qualitative variables, the Chi-square test or Fisher’s exact test will be utilized. Normality of quantitative variables will be assessed through the Kolmogorov-Smirnov and Shapiro-Wilk tests, as well as visual examination of distribution (histogram, QQ-plot, and box plot). If the distribution is found to deviate from normality, logarithmic transformation of the variable will be applied. Subsequently, univariate analysis of quantitative variables will be performed using the t-Student test. Statistical significance will be considered at P < 0.05, and conclusions will be drawn with support from confidence intervals whenever applicable.

The primary objective of the study will be analyzed through an ANCOVA, using the treatment group assignment as a covariate, to determine whether there is an equivalent effect among subgroups or not.

For the analysis of secondary objectives, a multilevel model will be employed, considering the hierarchical structure of the data due to the fact that one donor may contribute to multiple recipients, as well as the number of cycles.

Data will be entered into a database within our department and analyzed using statistical software packages SPSS version 22.0 for Windows (SPSS Inc., Chicago, IL) and R version 4.2.2 for Windows (R Foundation for Statistical Computing, Vienna, Austria).

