## Outcomes

The primary objective of this study is to compare the efficacy (non-inferiority) of the MNP protocol (Seidigestan®) to an antagonist protocol, using the number of mature metaphase II (MII) oocytes as the primary outcome variable.

Our secondary objectives are detailed in **Table 1**.

**Table 1 T1:** Secondary outcomes for comparison of oral progesterone vs GnRH antagonist.

Treatment	Analyzing and comparing the baseline characteristics of each group of donors
	Comparing the gonadotrophin dose and treatment duration
Laboratory	Fertilization rate per-oocyte injected
	Assessing whether there are differences in the performance of these MII oocytes in fresh cycles and their potential to develop into blastocysts after ICSI
Clinical	Documenting the fresh transfers of blastocysts originating from each protocol and the endometrial preparation protocols
	Biochemical pregnancy: a pregnancy diagnosed only by the detection of beta hCG in serum or urine, which fails to progress to the point of ultrasound confirmation
	Clinical pregnancy: an intrauterine pregnancy diagnosed by ultrasonography
	Ongoing pregnancy: the presence of a heartbeat as seen by ultrasonography 12 weeks gestation
	Multiple pregnancy: two or more gestational sacs seen by ultrasonography
	Early pregnancy loss: the spontaneous loss of an intrauterine pregnancy, where there is no fetal heartbeat detected at the time of ultrasound at 6–8 weeks
	Ectopic pregnancy: a pregnancy outside the uterine cavity, diagnosed by ultrasound, surgical visualization or histopathology
	Miscarriage: the spontaneous loss of an intrauterine pregnancy with fetal heartbeat prior to 20 completed weeks of gestational age
	Live birth: the complete expulsion or extraction from a woman of a product of fertilization, after 22 completed weeks of gestational age; which, after such separation, breathes or shows any other evidence of life, such as heartbeat, umbilical cord pulsation or definite movement of voluntary muscles, irrespective of whether the umbilical cord has been cut or the placenta is attached
	Analyzing possible obstetric differences between both protocols
Cost-effectiveness	Contrasting the economic cost per number of mature oocytes (MII) obtained in each treatment regimen
Quality of life	Women will also be asked to complete a survey consisting of questions related to treatment tolerability

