### Statistical analyses

#### Sample size

Considering an expected yield of 13.58 oocytes in the control group with a standard deviation of 6.997 (based on an internal study conducted within the clinic, encompassing all oocyte donor stimulations performed in 2021), and accepting an alpha risk of 0.05 and a beta risk of 0.20 in a one-sided test (with an 80% statistical power), a sample size of 136 patients (68 in each study group) is required to detect a minimum difference of 3 oocytes. Accounting for an estimated loss of 10%, a total sample size of 150 patients (75 per group) is needed.

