#### Analysis of secondary outcomes

The secondary objectives will be analyzed based on the nature of the variable under evaluation. Parametric tests, such as Student’s t-test, or non-parametric tests, such as the Wilcoxon-Mann-Whitney test for independent data, will be employed for secondary analyses comparing the two treatments, depending on the normality or non-normality of the quantitative data distribution. For categorical variables, the Chi-square test or Fisher’s exact test, as appropriate, will be used.

Secondary analyses will be conducted in the intention-to-treat (ITT) analysis population.

Given that randomization has been carried out with oocyte donors rather than recipients, caution must be exercised when interpreting the results for the latter. To mitigate potential biases and control for the possibility of a single donor contributing oocytes to multiple recipients, the impact of different treatments will be assessed using a multilevel analysis. This analysis will consider the hierarchical or nested structure of our data and will be multivariable, incorporating various covariates to control for potential biases.

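### The log-transformation rule for non-normal variables does not exempt the primary MII count, and so conflicts with the primary analysis and the 3-oocyte difference, both on the raw scale

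*Protocol article*

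**What the plan says.** The Outcomes section defines the primary comparison "using the number of mature metaphase II (MII) oocytes as the primary outcome variable".

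The Data analysis section sets a general sequence. First, "Normality of quantitative variables will be assessed through the Kolmogorov-Smirnov and Shapiro-Wilk tests", together with plots. Then: "If the distribution is found to deviate from normality, logarithmic transformation of the variable will be applied". Then: "Subsequently, univariate analysis of quantitative variables will be performed using the t-Student test". No variable is exempted, and nothing says which test or plot prevails when they disagree.

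The section Analysis of the primary outcome presents the primary variable as a mean number of oocytes with a 95% confidence interval, and compares the means by Student's t-test in the ITT population, repeated per protocol. It does not say what happens if normality is rejected.

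The Sample size section assumes an "expected yield of 13.58 oocytes in the control group", "with a standard deviation of 6.997", a one-sided alpha of 0.05 and 80% power. It concludes that 136 patients (68 per group) "is required to detect a minimum difference of 3 oocytes".

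The section Analysis of secondary outcomes handles non-normal data differently, by a non-parametric test "such as the Wilcoxon-Mann-Whitney test for independent data".

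**The concern.** The MII count is a quantitative variable, and its primary analysis uses the same t-test to which the general sequence leads. A reader applying the Data analysis section literally would log-transform it whenever normality is judged to fail. A reader applying the section on the primary outcome would keep it in oocytes. Both cannot be followed once the rule is triggered.

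In a non-inferiority trial the choice matters. On the log scale the treatment effect is a ratio of geometric means, and 3 oocytes has no fixed counterpart there. A donor with no mature oocytes has no logarithm. Such donors can occur: the protocol stops stimulation for poor response, and the primary population is ITT. What is being estimated, the effective margin and the handling of the worst outcomes would then depend on a distributional check made after the data are seen.

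**Working it through.** **1. The scale of the plan's own sample size.** Inputs from the Sample size section: SD 6.997, difference 3, one-sided alpha 0.05, power 0.80.

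n per arm = 2 × SD² × (z₀.₉₅ + z₀.₈₀)² / d² = 2 × 48.958 × (1.6449 + 0.8416)² / 9 = 67.3, rounded up to 68.

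This reproduces the stated 68 per group. The figure is a raw-scale difference in means and is not in error.

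**2. The same difference on the log scale.** Ratio = (control mean − 3) / control mean.

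| Control mean | Ratio equal to −3 oocytes |
|---|---|
| 10 | 0.70 |
| 13.58 | 0.779 |
| 16 | 0.81 |
| 20 | 0.85 |

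The ratio is 0.779 only if the control mean is exactly 13.58. The protocol states no ratio margin.

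**3. How often the rule would be triggered.** The protocol gives only a mean and an SD (coefficient of variation 6.997/13.58 = 0.52), so the shape is an assumption. Share of simulated trials (2,000 runs, N=150) in which Shapiro-Wilk rejects at 0.05:

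| Assumed shape, mean 13.58, SD 6.997 | Rejection |
|---|---|
| Normal, rounded and floored at 0 | about 25–27% |
| 5% zeros plus negative binomial | 75% |
| 10% zeros plus negative binomial | 99% |
| Negative binomial, size 13.58²/(48.958 − 13.58) = 5.21 | 99% |

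Rounded gamma and lognormal shapes give close to 100%. Kolmogorov-Smirnov without correction for estimated parameters rejects in 1% to 89% across these shapes, and the Lilliefors version in 24% to 100%. The named tests can therefore disagree.

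**4. Zeros.** Under the plain negative binomial, P(0) = 0.00125, so the chance of at least one zero among 150 donors is 1 − 0.99875¹⁵⁰, about 17%. If 5% of donors have none, it exceeds 99%. The protocol gives no zero rate.

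*If zeros are dropped:* 75 per arm, negative binomial counts (size 5.21) plus added zeros, one-sided 5%, ratio margin 0.779, and a true overall deficit of exactly 3 oocytes.

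| Added zeros, control vs progesterone | Non-inferiority falsely declared, log scale |
|---|---|
| no excess in the progesterone arm | about 5% |
| 5% vs 10% | 12% |
| 5% vs 15% | 28% |
| 5% vs 26% | 78% |

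In the last row the whole deficit comes from zero-yield donors. The result there ranges up to 86% with a smaller spread among the other donors. The untransformed Welch analysis with zeros kept stays near 5%.

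*If a constant is added instead:* at 68 per arm, 5% zeros in both arms and no true difference, power with the 0.779 margin is 0.65 for log(x+1), 0.54 for log(x+0.5) and 0.37 for log(x+0.1), against 0.80 untransformed.

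**5. The opposite direction.** With equal arithmetic means but more dispersion in the progesterone arm (negative binomial size × 0.6), non-inferiority is shown in 76% of trials untransformed and 54% on the log scale.

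**6. Whether the transformation is needed.** It is not. For skewed counts at 68 per arm, with 0%, 5% or 10% zeros, the raw-scale test has power of about 0.80 and type I error of 0.051 to 0.055. At 75 per arm, power is about 0.83. The log step may not restore normality either: log(x+1) is still rejected in 82% of negative binomial trials.

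**The case against.** The strongest reply is that the section on the primary outcome governs. It is the specific text, it speaks of mean numbers of oocytes, and it matches the raw-scale difference in the sample size. By the usual rule that specific text overrides general text, the primary analysis already is a difference in means, and the log rule serves only the general univariate comparisons. This has force. A reader might infer that the plan moves the primary analysis to the log scale, and the documents do not support that; they support a conflict between two sections. The conflict stands, because the general rule covers all quantitative variables, leads to the same t-test, and names no exception.

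Three further points also limit the concern:

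- **Trigger.** A reader might infer that the rule will probably be triggered. That depends on a shape the protocol does not give, and on tests and plots whose precedence it does not state.
- **Zeros.** A reader might infer that zero-yield donors will be dropped. The protocol never says so. An added constant is another possibility, and such handling may be left to an analysis plan not shown here. The absence of a zero rule is not in itself the finding.
- **Direction.** A reader might infer that the log route always favours progesterone. Large false-positive rates need a large excess of zeros in that arm, and the 78% case is deliberately extreme. Unequal dispersion works the other way.

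**Conclusion.** The concern holds as an internal conflict. A stated rule, read as written, covers the primary endpoint and would yield a contrast for which no margin is given and which is undefined for donors with zero MII oocytes. This is more than missing detail, because the rule could change the trial's primary conclusion in either direction.

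The conflict itself is certain from the text. Its consequences are conditional: the 25% to 99% trigger range rests on assumed shapes and on Shapiro-Wilk alone, and the rise in false non-inferiority from about 5% to 28% rests on assumed zero rates and on zeros being dropped. Reading 3 oocytes as the non-inferiority margin is also an inference, from the non-inferiority design and the reproduced sample size; the protocol words it as a difference to detect.

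**What to change.** State that the primary endpoint is exempt from the transformation rule. Analyse the untransformed MII count in all randomized donors, zeros included, as a difference in arithmetic means (progesterone minus antagonist), with a Welch or robust-standard-error confidence interval compared with −3 oocytes. For non-normal secondary variables, choose either transformation or a non-parametric test, and state the same rule under both Data analysis and Analysis of secondary outcomes.

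The cost is wording only. The sample size already rests on the raw scale and does not change.

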#### Analysis of the primary outcome

The analysis of the primary variable will be presented as the mean number of oocytes along with its corresponding 95% confidence interval. Student’s t-test will be used to compare the mean number of oocytes between each group. A multivariate linear model will be adjusted for the number of oocytes, incorporating the group and potentially confounding variables. A variable selection process using stepwise selection based on the AIC (Akaike Information Criterion) will be conducted.

The primary analysis will be performed in the intention-to-treat (ITT) analysis population and will also be repeated in the per-protocol (PP) analysis population.

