## Abstract

**Introduction:**

Progesterone-primed cycles effectively suppress the pituitary LH surge during ovarian stimulation in oocyte donors and in the infertile population. Particularly in oocyte donors, the use of synthetic progesterone (progestins) has been explored in prospective clinical trials, showing mixed results. This trial was designed to determine whether the use of micronized natural progesterone is as effective as the GnRH-antagonist protocol in terms of the number of mature oocytes (MII) retrieved in oocyte donation cycles as a primary outcome, and it also aims to explore the corresponding results in recipients as a secondary outcome.

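### The trial is declared non-inferiority, but its primary analysis is a t-test with a P < 0.05 criterion that never uses the 3 oocytes, and no rule says when non-inferiority is concluded

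*Protocol article*

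**What the plan says.** All references are to the protocol article.

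- **Objective.** The Abstract (Methods), Outcomes and Study design each declare a non-inferiority trial. Outcomes states: "The primary objective of this study is to compare the efficacy (non-inferiority) of the MNP protocol (Seidigestan®) to an antagonist protocol". The Abstract's introduction puts the question as "whether the use of micronized natural progesterone is as effective as the GnRH-antagonist protocol in terms of the number of mature oocytes (MII) retrieved".
- **Sample size.** The inputs are a control mean of 13.58, an SD of 6.997, a one-sided alpha of 0.05 and 80% power. The result, 136 donors (68 per group), "is required to detect a minimum difference of 3 oocytes". It is raised to 150 (75 per group) for a 10% loss. The 3 oocytes appear nowhere else, and they are not called a margin.
- **Data analysis.** "Statistical significance will be considered at P < 0.05", with confidence intervals in support where applicable. The primary objective is assigned to an ANCOVA meant to show whether the effect is equivalent among subgroups. Variables that depart from normality are to be log-transformed.
- **Analysis of the primary outcome.** The mean number of oocytes is presented with a 95% CI. Student's "t-test will be used to compare the mean number of oocytes between each group". A linear model with AIC-based stepwise selection follows. The analysis is done in ITT and repeated in PP.

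**The concern.** A non-inferiority conclusion needs a margin and a rule that sets a confidence limit for the between-arm difference against it. The design section has a figure that could serve as the margin. The analysis sections never use it, and the three procedures they name (t-test, ANCOVA, stepwise model) come with no non-inferiority hypothesis.

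A test of zero difference does not answer the stated question in either direction. A P value above 0.05 is compatible with a deficit larger than 3 oocytes. A P value below 0.05 against progesterone does not refute non-inferiority if the interval stays above -3.

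The trial's main conclusion is at stake. With P < 0.05 as the only written criterion and an as-effective-as question to answer, nothing in the text prevents a non-significant result from being reported as success.

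**Working it through.** **Inputs.** From Sample size: difference 3 oocytes, SD 6.997 (taken as equal in both arms), one-sided alpha 0.05, power 80%, 68 evaluable and 75 randomised per arm. From Data analysis: criterion P < 0.05. The article does not state the sidedness of the primary t-test, so both cases are shown.

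**1. Reproduce the stated size.** With margin 3 and an assumed true difference of 0:

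n per arm = 2 × SD² × (z₀.₉₅ + z₀.₈₀)² / 3² = 2 × 6.997² × (1.645 + 0.842)² / 9 = 67.26, rounded up to 68.

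This matches the article. The noncentral t gives 80.0% power at 68 per arm. A one-sided superiority calculation for a difference of 3 also gives 68, so the arithmetic fits a margin of 3 but does not by itself prove that 3 was meant as one.

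**2. Standard error and half-widths.** SE = 6.997 × √(2/n).

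| Per arm | SE | Half-width, 95% CI | Half-width, 90% CI |
|---|---|---|---|
| 68 | 1.200 | 2.37 | 1.99 |
| 75 | 1.143 | 2.26 | 1.89 |

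**3. How often a true deficit of 3 gives a non-significant test.** This uses the noncentral t with noncentrality 3/SE, which is 2.50 at 68 per arm and 2.63 at 75 per arm.

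| Per arm | Two-sided t-test, P ≥ 0.05 | One-sided t-test, P ≥ 0.05 | Margin test at one-sided 0.05 |
|---|---|---|---|
| 68 | 30.1% | 20.0% | 5% |
| 75 | 25.8% | 16.6% | 5% |

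**4. Where the two readings part.** At 75 per arm, a two-sided test is non-significant for any observed deficit below 2.26. Non-inferiority at one-sided 0.05 needs an observed deficit below 3 − 1.89 = 1.11. Observed deficits from 1.11 to 2.26 are therefore not significant and also not non-inferior. If the lower limit of the 95% CI is used, the range starts at 3 − 2.26 = 0.74.

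Example: an observed deficit of 2.0 at 75 per arm gives P = 0.08, a 95% CI of -4.26 to 0.26 and a 90% CI of -3.89 to -0.11. Both intervals extend below -3.

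**5. Power of a margin rule (true difference 0, noncentral t).**

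| Rule: lower limit above -3 | 68 per arm | 75 per arm |
|---|---|---|
| One-sided 95% limit (two-sided 90% CI) | 80.0% | 83.4% |
| Lower limit of two-sided 95% CI | 69.9% | 74.2% |

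With the two-sided 95% CI, 80% power needs about 86 evaluable donors per arm by the formula in step 1: 2 × 6.997² × (1.960 + 0.842)² / 9 = 85.4.

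**The case against.** **The t-test's null is not stated.** A t-test against a null shifted by 3 is still a Student's t-test, and Sample size does specify a one-sided test. This stands in part: the article does not say in so many words that it tests zero difference. But it gives no shifted null, and P < 0.05 on a comparison of two means is ordinarily read as a test of zero difference. The unstated sidedness is why the size is given as a range.

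**No step to a false conclusion is written.** A reader might infer that the plan will declare progesterone as effective whenever the test is non-significant. The documents do not support that: no sentence says so. The rates in step 3 describe what that reading would do, not a rule the sponsor has adopted.

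**Confidence intervals are mentioned.** They are, as support. But the interval in Analysis of the primary outcome is for the mean number of oocytes, not clearly for the difference, and no interval is tied to -3.

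**The margin is inferred.** This stands. The text says a difference to detect, and the sample-size arithmetic fits superiority as well. The declared design makes a margin of 3 the natural reading, but the sponsor has to confirm it.

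**A fuller SAP may exist.** The confidence level and the exact success rule could have been left to it, and their absence alone would not be a finding. But the article fixes the primary test itself, and that test does not match the declared objective. A SAP that used the margin would have to depart from this text.

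**Conclusion.** The point holds as a mismatch between objective and analysis. The article declares non-inferiority, fixes a primary t-test with a P < 0.05 criterion, uses the 3 oocytes in no analysis, and states no rule for concluding non-inferiority. It must be corrected, because the primary conclusion depends on a rule that is not there.

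The size is conditional. If non-significance were taken as non-inferiority, a true deficit of 3 oocytes would pass 26% to 30% of the time (two-sided) or 17% to 20% (one-sided), three to six times the 5% in Sample size. This assumes an SD of 6.997 in both arms and 68 to 75 analysed donors per arm.

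It would go too far to say that the trial is mis-sized. With 3 as the margin, a true difference of 0 and a one-sided alpha of 0.05, the stated 68 per arm is right.

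**What to change.** 1. In Sample size, name 3 oocytes as the non-inferiority margin, with an assumed true difference of 0.
2. In Analysis of the primary outcome, replace the t-test sentence with:

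> Non-inferiority is concluded if the lower one-sided 95% confidence limit (the lower limit of the two-sided 90% CI) for the mean difference in MII oocytes, MNP minus antagonist, on the untransformed scale, lies above -3 in the ITT population and consistently in the PP population.

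3. Keep the test of zero difference only as a follow-on superiority test.

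The untransformed scale has to be stated because Data analysis calls for a log transformation when normality fails, and an absolute margin of 3 oocytes does not carry over to the log scale. The text should also say which of the t-test, the ANCOVA and the stepwise model supplies the difference and its limit.

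**Cost.** At the one-sided 95% level this is a wording change with no extra donors or data: power is about 80% at 68 per arm and 83% at 75 per arm. If the sponsor prefers the two-sided 95% CI already named in the article, the stated power must be restated as about 70% at 68 per arm or 74% at 75 per arm. Keeping 80% would then take about 86 evaluable donors per arm.

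### The plan does not say whether the unadjusted or the stepwise-adjusted comparison decides non-inferiority on MII oocytes; one ANCOVA with fixed baseline covariates should be named as primary

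*Protocol article*

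**What the plan says.** The Outcomes section sets the aim: "The primary objective of this study is to compare the efficacy (non-inferiority) of the MNP protocol (Seidigestan®) to an antagonist protocol", with MII count as the outcome variable. The methods for that outcome then appear in two places under Statistical analyses.

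- **Data analysis:** "The primary objective of the study will be analyzed through an ANCOVA, using the treatment group assignment as a covariate". No baseline covariate is named, and the stated purpose is worded as equivalence across subgroups.
- **Analysis of the primary outcome:** "Student’s t-test will be used to compare the mean number of oocytes between each group". Next comes "A multivariate linear model will be adjusted for the number of oocytes, incorporating the group and potentially confounding variables", and then "A variable selection process using stepwise selection based on the AIC (Akaike Information Criterion) will be conducted".

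The same section says that the primary analysis is run in the ITT population and repeated in the PP population, but not which comparison the primary analysis is. Table 1 lists as a secondary outcome "Comparing the gonadotrophin dose and treatment duration". The section on oocyte donors and ovarian stimulation lets physicians change the gonadotropin dose during stimulation.

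**The concern.** A non-inferiority conclusion needs one estimate and one confidence bound, fixed in advance. Here an unadjusted and an adjusted estimate are both attached to the primary outcome with no order between them, and the covariates in the adjusted one depend on the data. If the two fall on opposite sides of the margin, the text does not say which counts.

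Two gaps in the selection rule add to this. The wording does not exempt the group term, so a literal stepwise run could remove it. Nor does it confine the candidates to baseline. Gonadotrophin dose and treatment duration are determined after randomisation, and adjusting for them would change the question being answered.

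Covariates in a randomised trial serve precision, and a fixed list delivers that without a selection step. The description of the ANCOVA also needs repair. Group is the factor under test, not a covariate. A model with group alone is the t-test, and without interaction terms it says nothing about subgroups.

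**Working it through.** **Inputs.** From Sample size: SD 6.997, difference 3 oocytes (read here as the margin), one-sided alpha 0.05, power 0.80, 68 evaluable per arm, 75 recruited. Assumed, because the article gives no figure: the share of variance explained by baseline covariates (R²), taken as 0.1 to 0.3.

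**1. The plan's own figure.** For a true difference of 0:

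n per arm = 2 × 6.997² × (1.645 + 0.842)² / 3² = 67.3, so 68 per arm and 136 in total. This matches. The calculation is for an unadjusted comparison.

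**2. How many distinct analyses there are.** If group is the only term in the ANCOVA, it is the t-test. If the ANCOVA is meant to carry the confounders, it is the linear model. Either way two comparisons remain, one unadjusted and one stepwise-adjusted.

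**3. Error rate at a true deficit of 3 oocytes.** Simulation with 68 per arm, 3,000 runs, one real baseline predictor and six noise candidates, success when the one-sided 95% lower bound exceeds −3:

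| Analysis | R² = 0.1 | R² = 0.3 |
|---|---|---|
| t-test | 0.053 | 0.054 |
| ANCOVA, fixed covariate | 0.054 | 0.056 |
| Stepwise AIC, group kept | 0.060 | 0.062 |
| Any of the three may be used | 0.073 | 0.085 |

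The Monte Carlo standard error near 0.05 is √(0.05 × 0.95 / 3000) = 0.004, so the excess from selection alone is slight. The last row also counts the fixed ANCOVA. A 6,000-run repeat allowing only the t-test or the stepwise model gave 0.066 and 0.085, so the choice between two analyses accounts for nearly all of it.

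**4. If group were open to selection.** In a group-only model AIC drops a one-degree-of-freedom term when |z| is below √2. At no true difference the probability is 2Φ(1.414) − 1 = 0.84. At 68 per arm the standard error is 6.997 × √(2/68) = 1.200, and the non-central t distribution gives:

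| True difference | Probability that group is dropped |
|---|---|
| 0 | 0.84 |
| −1 | 0.70 |
| −2 | 0.40 |
| −3 | 0.14 |

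Group could be dropped with an observed deficit of up to 1.41 × 1.200 = 1.69 oocytes. The one-sided 95% lower bound there is about −3.68, which fails a margin of 3.

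**5. If a variable affected by treatment entered.** Suppose it carried 25% or 50% of a true −3 effect in the same direction (assumed shares). The mean estimate would shrink to −2.3 or −1.5, and false non-inferiority would be about 0.17 or 0.44. An opposite pathway would move the estimate the other way.

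**6. Gain from a fixed baseline set.** Power = Φ(3/SE − 1.645), with SE = 6.997 × √(1 − R²) × √(2/68):

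| R² | SE | 3/SE − 1.645 | Power |
|---|---|---|---|
| 0 | 1.200 | 0.855 | 0.804 |
| 0.1 | 1.138 | 0.990 | 0.839 |
| 0.2 | 1.073 | 1.150 | 0.875 |
| 0.3 | 1.004 | 1.343 | 0.910 |

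**The case against.** The strongest defence is that the text describes an ordinary pair, a crude comparison and an adjusted one, and that the candidate list belongs in a SAP or full protocol that is not shown. Several parts of that defence stand.

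- A reader might infer three competing models that could give three answers. Step 2 shows that there are two.
- A reader might infer that AIC will delete the treatment effect. The linear model is described as including group, and the natural reading is that selection applies to the confounders. The 84% therefore holds only on the opposite reading, and only for a model with no covariates.
- A reader might infer that a dropped group term would leave no effect estimate. The t-test is carried out whatever AIC does, so an unadjusted comparison always exists.
- A reader might infer that dose or duration will be adjusted for, with bias towards no difference. Neither is named as a candidate, and the Discussion's own example of a confounder is age, a baseline variable. The direction is also open. The Discussion cites a retrospective comparison with a short agonist protocol in which progesterone cycles needed longer stimulation and more gonadotropin. If extra stimulation offsets a deficit, adjusting for it would enlarge the estimated deficit.
- Stepwise selection would usually keep strong baseline predictors, so part of the precision gain in step 6 could arise under the present plan too.

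The defence does not answer the core. The missing order between the two analyses is a conflict within the text, not detail left for later. Stepwise AIC is a stated commitment, which a SAP would have to overrule rather than complete.

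**Conclusion.** The point holds in a limited form. The article attaches an unadjusted and a data-selected adjusted comparison to one non-inferiority question without saying which decides, and its selection rule neither protects group nor restricts candidates to baseline.

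On the charitable reading (group kept, baseline candidates only) selection by itself costs about one percentage point of type I error. Free choice between the analyses costs about two to four points. These figures rest on a simulation with normal data and an assumed set of candidates. The larger effects in steps 4 and 5 depend on readings that the wording allows but does not state, and the mediated shares in step 5 have no support in the document. They are reasons to close the gaps, not predictions of what will happen.

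The sample size of 136 is unaffected. This is a near-free improvement that should be made, not a flaw that invalidates the design.

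**What to change.** 1. Name one primary analysis: an ANCOVA of MII count, on the oocyte scale, on treatment group plus a short fixed list of baseline covariates, with group always retained. AFC, age, BMI and centre are examples. The first three are eligibility data, AFC also guides the starting dose, and centre is known for every donor.
2. Decide non-inferiority by comparing the confidence bound for the adjusted difference with the 3-oocyte margin, and state that this is the analysis run in ITT and repeated in PP.
3. Delete stepwise AIC selection and exclude post-randomisation variables, including gonadotrophin dose and treatment duration, from the primary model.
4. Keep the t-test as a sensitivity analysis.
5. In Data analysis, replace "will be analyzed through an ANCOVA, using the treatment group assignment as a covariate" with wording that makes group the factor being compared, and replace the subgroup-equivalence aim with the non-inferiority comparison.

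The cost is a change of wording and a few degrees of freedom, with no extra donors or data. The change should be made before outcome data are seen.
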